### **Summary of Study**

**Significance and justification:** The 2018 WHO Nurturing Care Framework calls on governments to provide interventions for families to support responsive caregiving and early learning for children 0-3 years. The Ministry of Health and Wellness plans to implement the Reach Up early childhood parenting programme through health centres in Jamaica. Initial evaluation of the implementation utilizing remote delivery methods showed benefits to parent practices and was acceptable to the parents and health staff. In this phase of implementation, we will assess the impact on child development and parenting practices when implemented at larger scale.

**Study Design:** The intervention will be implemented using a blended approach (home visits and phone calls) in one health district per parish over an 8-month period. Caregivers will receive a parent manual of play activities and a few play materials. Caregivers will also receive weekly text messages to encourage them to continue the activities with the child. Impact evaluations will be conducted in all parishes, within the health districts participating in the study. Trained community health aides (CHAs) will conduct fortnightly intervention contacts (one home visit and one phone call alternately). Each CHA will be assigned 8 families, with 4 randomly assigned to intervention and 4 to the waitlist group. With approximately 8 CHAs per district, sample size will be 416 in intervention and 416 in comparison (wait list) groups.

Baseline questionnaires will be administered to obtain information on family and maternal characteristics. Impact evaluation, including assessment of child development and parenting behaviours will be conducted after the 8-month intervention period.

**Benefits and Risks:** There are no specific benefits to participants. The risks to participants are minimal.

**Confidentiality:** All questionnaires and child assessments will be conducted in private with the child and parent. Participants will be identified by their ID number only on all study documents.

The best interest of the participants will be respected at all times, and they will be provided maximum protection.

### **Introduction and Justification**

Target 4.2 of the Sustainable Development Goals calls for all children to have access to quality early childhood development and care by 2030, and the recent child development Lancet series highlights the need for early child development interventions to be integrated into government services [1]. At the World Health Assembly, in May 2018 the WHO launched the Nurturing Care Framework that places responsive caregiving and opportunities to learn for children 0-3 years as critical components of care for young children and calls on government to provide necessary support and services for families who are the primary providers of care for young children.

The Jamaican early childhood home visiting (JHV) intervention is based on strengthening the capacity of mothers and other caregivers to promote optimal development of their children, through responsive interactions and play activities. The intervention has substantial benefits for child development and has been shown to be feasible for implementation through health services [2, 3]. The intervention is delivered through home visits by community workers and has been implemented in several countries with consistent benefits for children's cognition and language development [4]. In one longitudinal follow up substantial long- term benefits to cognition, education, mental health and income have been found at 17 and 22 years of age [5-7]. This work has been highly influential in policy in global child development.

The JHV has formed the basis for the Reach Up early childhood parenting programme. Reach Up was developed in order to increase capacity for implementation of early childhood parenting programmes in other countries and for larger numbers of families. Programme content includes a weekly and fortnightly curriculum, training manuals for supervisors and visitors including videos, and manuals on toy making, implementation planning and adaptation. The programme has now been implemented in several countries including Bangladesh [8, 9], India [10], Zimbabwe, China, Colombia [11], Brazil, Bolivia, and Peru [12]. Reach Up has been shown to be well accepted and feasible [13].

The Jamaica Ministry of Health and Wellness (MOHW) plans to implement Reach Up in all parishes in Jamaica. Implementation will be through a phased roll out beginning in one health district per parish. The intervention will be implemented on a fortnightly basis and will be conducted through the health centres in each district. We propose to use this phase of implementation to evaluate the impact of the intervention on child development and parenting when implemented at larger scale.

### **Research Questions**

Impact evaluation: What are the benefits to child development and behaviour when the Reach Up programme is delivered through government primary health care services in Jamaica?

### **Methods**

### *Selection of districts and sample*

Each Parish health team, led by the Medical Officer of Health, nominated the health district within the parish for the initial implementation phase (phase 1) and two nurses to be trained in the intervention. Initial impact and implementation evaluations were conducted in six parishes that began home visits before these were suspended in March 2020. Remote delivery was conducted in these parishes beginning in September 2020 and evaluated from July to October 2021. Feedback from health staff and families suggested the use of a blended intervention with home visits and phone calls. In this phase of the study the impact of the blended intervention on child development and parent practices will be evaluated.

The intervention will focus on children aged 6-24 months who meet at least one of the following criteria: families where the child or mother is registered with the Programme of Advancement through Health and Education (PATH) or the family resides in a low income setting. Children identified and whose mother provides consent to participate will be randomly assigned to either receive the intervention now or after 8 months (wait list group). Children assigned to the 'wait list' group will continue to receive usual care from the health centres.

Within each district the intervention will be implemented in 1-3 health centres that will comprise those supervised by the nurses trained. All community health aides (CHAs) assigned to these health centres will be trained to deliver the intervention, approximately 8 CHAs per district. So as to enable the CHAs to conduct the fortnightly intervention contacts (home visits and phone calls) together with their usual duties, each CHA will be assigned 8 families with 4 randomly assigned to intervention and 4 to the waitlist group. We therefore estimate 32 children in the intervention group per district and another 32 children per district in the wait list group, with a total of 416 per group across all parishes.

Mother-child pairs will be excluded if:

- Child is in Daycare or has no consistent caregiver
- The baby has major disability likely to affect development

Sample size calculation: From prior work we estimate an effect size for the primary outcome of child developmental quotient of 0.3SD (3.6 points) and SD of 12 points. For 80% power and significance level of  $p < 0.05$ , this gives a sample size per group of 178. The actual proposed sample per group of 416 allows for possible lower recruitment levels in some districts and 10% loss to follow-up at endline. It will also allow for analysis of moderators of impact as indicated in the analysis section.

We will obtain baseline information on maternal, family and child characteristics to demonstrate equivalence among intervention arms and enable us to control for any possible

confounders at post-test. The blended intervention will continue for 8 months, and post intervention measurements will then be conducted.

### *Description of intervention*

The blended intervention comprises fortnightly contacts with home visits and phone calls, conducted alternately, that will be delivered by CHAs for 8 months. Caregivers will receive a parent manual with play activities and a few materials. They will also receive weekly text messages that will provide encouragement to continue doing the activities with their child. The intervention works through parents by building a positive relationship to support them in strengthening skills to promote child development. The aims are to build mothers' skills, self-esteem and enjoyment in helping her child learn, through interactive play and responsive interactions. The intervention uses a structured curriculum with activities arranged in order of difficulty; children usually move on to the next set of activities with each contact.

The contacts begin with some time catching up with how the family has been and how the mother and child have progressed with the activities from the last visit. The CHA then engages the mother and child in a play session. In home visits new activities are introduced through an interactive approach: observing what the child does, demonstrating and describing the activity to mother and child, helping the child with the activity, encouraging mother and child to practise, giving positive feedback and celebrating success. Mothers are encouraged to respond to their child's vocalisations and actions. CHAs demonstrate ways to talk about and show her child objects and activities in their environment. The visitors promote giving praise, celebrating the child's achievements and efforts, and showing love throughout the visit. The visit ends with a review of activities to continue during the next two weeks and encouragement to continue the activities and to try and include them in daily routines. A similar approach is used in the phone-calls guided by a script. In this case the CHA asks the mother to try the activity with the child and to let her know what the child does. Further description and explanation are given where necessary.

CHAs will receive supervised visits or observations of the phone calls to provide supportive feedback and address any issues during the intervention period. Supervisors will use an evaluation checklist to assess the quality of the visit and the phone calls (contacts). The quality of the contact includes assessment of the interaction between the home visitor, mother and child; the atmosphere of the contact and the preparation of the home visitor for contact. Supervision will be conducted by nurses, health education officers and nutritionists.

### Implementation plan/framework

The blended intervention will be implemented in one health district per parish. Training and recruitment will be done in parishes sequentially with implementation beginning as soon as recruitment in that parish is complete. Nurses from the health centres will be given training as intervention supervisors. The CHAs will also receive training in the Reach Up blended intervention and following random assignment by an independent statistician CHAs will be assigned their families by the supervisors.

#### **Staff Training**

The MOHW trained health staff including nurses, health education officers and nutritionists to supervise the CHAs and support initial programme delivery. Training workshops were conducted in phases with the nurses (Public Health Nurses and Midwives), nutritionists and health education officers being trained first. These training workshops were conducted by the UWI Reach Up team (Drs [name], [name] and [name]). The nurses, nutritionists and health education officers also received specific training on supervision and how to use the checklist provided. The CHAs were trained in separate workshops conducted by the nurses, nutritionists and health educators who were previously trained with support from the Reach Up team.

For the blended intervention delivery, 2-day training workshops will be conducted by the UWI team with the health staff (nurses and CHAs). The staff will be trained on how to conduct the phone calls and home visits using a new combined curriculum and several of the home visit intervention methodologies will also be reviewed. Nurses, health educators and nutritionists will also be trained on how to use the Observation checklist when they supervise the phone calls and visits.

#### **Impact evaluation**

Baseline measurements will be collected on enrolment to the study to obtain information on family, maternal characteristics, mother's attitudes on child development and parent practices. Impact evaluation will be conducted at the end of the 8-month intervention period.

#### *Measurements*

Baseline - An interviewer administered questionnaire will be used to obtain information from the mother on the following (Appendix 1):

Maternal and family data: including mother's age and education, employment, family structure, standard of housing (crowding- person/room, type of toilet, water supply and household possessions). Information on father's age and presence in the home will also be obtained by maternal report. We will use a questionnaire previously used in Jamaica [14].

Attitudes on child development: mother's attitude concerning child development and her role in promoting child development, using a questionnaire previously used in Jamaica [14].

Parent Practices: questions from the Family Care Indicators questionnaire will be used to assess the activities the mother or principal caretaker does with the child [15]. The FCI has been modified for use in Jamaica and was used in the evaluation of the remote delivery intervention.

Maternal depressive symptoms: measures will be obtained by interview using the Brief Center for Epidemiological Studies-Depression (CES-D-10) scale[16]. The CES-D has been used previously in Jamaica [14].

Child: Date of birth and birth weight, current length and weight, will be obtained from the children's clinic records/ child passport.

End of intervention: The following sections of the questionnaire will be repeated – Attitudes on child development, parent practices and maternal depressive symptoms. Child development will be assessed with the Griffith Scales of Development [17] which have been used in several studies in Jamaica.

Checklist, observations

Evaluation Checklist: Supervisors will use an evaluation checklist to assess the quality of the visit or call. The quality of the visit or call includes assessment of the interaction between the home visitor, mother and child; the atmosphere of the visit and the preparation of the home visitor for the visit [18]. This checklist was developed previously in Jamaica and has also been used to monitor quality in other countries [18]. **(Appendix 1)**

## **Ethical Issues**

Impact Evaluation

Recruitment

The participants will be recruited from health centres in all parishes in Jamaica. Parents and children in the control group will continue to receive usual care and will receive the intervention at the end of this phase (8 months later). The evaluation sampling will ensure that there is no bias in selection of mothers to participate in the evaluation. The participants will be selected only because of the intervention under evaluation and not because of easy availability, diminished autonomy or social bias.

## Informed Consent

Interviewers will obtain informed consent from each participant before administering the questionnaire. Participants will be informed about the study and advised that participation is voluntary and they would be able to withdraw at any time. We would also inform them that all information collected will be kept confidential. **(Appendix 2)**

## Confidentiality

Questionnaires will not include the names of the mother or child to maintain confidentiality. All completed questionnaires will be kept safely in a locked file cabinet and access will be limited to research staff only. Locator information with participant names and addresses will be kept separate from the study data.

## Justice

Subjects will be selected only because they attend the health centres or have certain demographic characteristics that are relevant to the objectives of this study and not because of easy availability, diminished autonomy or social bias.

## Benefits

There are no direct benefits to participants, however information collected will be used to inform interventions and policy for child development in Jamaica, particularly the continued roll out of the Reach Up programme.

## Risks

There are minimal risks associated with the administration of the questionnaire or conducting the measurements.

## **Data Analysis Plan:**

### **Impact evaluation**

Primary analyses for the impact evaluation will be by intention to treat. We will compare the groups on baseline measurements and will control for any measures which differ among the groups at endline in multivariate analyses of outcome.

Following the primary regression analyses we will investigate whether impact varies by maternal characteristics (education, depressive symptoms) or child characteristics (age on enrolment). We will also investigate the mechanism for impact to determine if change in parent practices mediates the impact on child outcomes.

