## **Statistical analysis plan**

### **Data Analysis Plan** (on page 8 of the Trial protocol)

#### **Impact evaluation**

Primary analyses for the impact evaluation will be by intention to treat. We will compare the groups on baseline measurements and will control for any measures which differ among the groups at endline in multivariate analyses of outcome.

Following the primary regression analyses we will investigate whether impact varies by maternal characteristics (education, depressive symptoms) or child characteristics (age on enrolment). We will also investigate the mechanism for impact to determine if change in parent practices mediates the impact on child outcomes.

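### The covariate rule lets observed group differences choose the outcome model; fix the baseline covariates in advance and clarify 'at endline'

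*Protocol*

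**What the plan says.** The Data Analysis Plan (Impact evaluation) promises an intention-to-treat primary analysis and then gives one covariate rule: the arms are compared at baseline, and the analysis "will control for any measures which differ among the groups at endline in multivariate analyses of outcome". The same paragraph appears again at the end of the document under the heading Statistical analysis plan. Neither place names a covariate or says what counts as a difference.

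The Methods (Selection of districts and sample, sample size paragraph) explain why baseline data are collected: "to demonstrate equivalence among intervention arms and enable us to control for any possible" confounders at post-test.

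Under Measurements, three questionnaire sections given at baseline are repeated at the end of the intervention: "Attitudes on child development, parent practices and maternal depressive symptoms". The primary instrument appears only in the end-of-intervention list: "Child development will be assessed with the Griffith Scales of Development".

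After the primary regressions, the plan will "determine if change in parent practices mediates the impact on child outcomes".

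**The concern.** This is a stated rule, not a detail left for later, and any fuller analysis plan would have to contradict it. Each community health aide (CHA) has eight families, four randomised to each arm, so any difference between arms at enrolment is chance. A rule that adjusts for what differs lets that chance choose the model. It also selects on the wrong property: imbalance says nothing about how well a variable predicts the outcome, so a strong predictor that happens to be balanced is left out. The stated aim of showing equivalence follows the same logic, since finding no difference does not establish equivalence.

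Three things are at stake:

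- the primary model is not known until data are seen;
- outcomes measured twice usually lose the precision that their own baseline value would give;
- 'at endline' can be attached to 'differ', which would admit endline measures that the programme is meant to change.

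**Working it through.** **Inputs from the Protocol.** Effect and SD: "an effect size for the primary outcome of child developmental quotient of 0.3SD (3.6 points) and SD of 12 points". 80% power, p<0.05, a calculated 178 per group, 416 per group planned, 10% loss to follow-up, 1:1 allocation. Two-sided testing is assumed because it reproduces the stated sample size.

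**Inputs assumed, because the Protocol does not give them.** Selection of a covariate when its baseline t-test has p<0.05; a 0.2 SD effect on the repeated measures; baseline–endline correlation r of 0.3, 0.5 or 0.6.

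**1. The plan's own figure.** n = 2(1.960 + 0.842)² / 0.3² = 174.4, so 175 per group (176 with the t distribution). This agrees with 178 to within 3%. A one-sided test would give 138. The sample size is not in dispute.

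**2. Number analysed.** 416 × 0.90 = 374 per arm, if recruitment is full.

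**3. How often a covariate is selected.** Under randomisation a given baseline measure passes p<0.05 about 5% of the time (4.8–5.5% in simulation). An outcome's own baseline value is therefore left out about 95% of the time. The chance that at least one of k independent measures is selected is 1 − 0.95^k: 40% for k = 10 and 64% for k = 20. Correlated measures, such as the housing items, would lower this.

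**4. Cost for the three repeated measures.** In SD units the unadjusted standard error is √(2/374) = 0.073. Always adjusting for the baseline value multiplies it by √(1 − r²). Simulation (4,000 runs per setting) gave:

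| r | SE, rule | SE, always adjusted | Power, rule | Power, always adjusted | Type I error, rule |
|---|---|---|---|---|---|
| 0.3 | 0.073 | 0.070 | 78% | 82% | 5.1% |
| 0.5 | 0.073 | 0.063 | 79% | 88% | 4.1% |
| 0.6 | 0.072 | 0.059 | 80% | 93% | 4.8% |

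The formula agrees: at r = 0.5, 0.073 × √0.75 = 0.063.

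**5. Primary outcome.** No baseline Griffiths score is listed, so the table does not apply to it. Power for 3.6 points with SD 12 is 81% at 178 per group, 98.4% at 374 and 99.1% at 416. If other baseline covariates explained 10–20% of the variance (assumed), power at 374 would rise from 98.4% to about 99.1–99.6%.

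**6. The literal reading of 'at endline'.** Suppose the programme raises endline practices by a SD and practices relate to the developmental quotient with slope b. Adjusting for endline practices then leaves 0.3 − ab of a true 0.3 SD effect. Assumed values a = 0.3–0.5 and b = 0.2–0.4 give:

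- mildest: 0.3 − 0.3 × 0.2 = 0.24 SD, or 2.9 points;
- strongest: 0.3 − 0.5 × 0.4 = 0.10 SD, or 1.2 points.

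In simulation (2,000 runs per setting) practices were selected in 98–100% of trials, and power fell from 98% to between 91% and 31%.

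**The case against.** The strongest reply is that the sentence is loosely written but benign. It opens with a comparison on baseline measurements, and the Methods say baseline data serve to control confounders at post-test. The natural meaning is therefore baseline measures that differ, controlled for in the endline analysis. It could also mean baseline measures that differ among those retained at endline. The plan handles change in parent practices separately, as a mediation question after the primary regressions; adjusting for it in the primary model would defeat that step. A covariate list is also often left to a separate analysis plan. Much of this stands.

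A reader might draw three stronger inferences that the documents do not support:

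- **That the plan intends to adjust for mediators, so the primary estimate is biased.** The text permits this but makes it the less likely meaning. It is an ambiguity to close.
- **That the rule inflates false positives.** With one candidate covariate, simulated type I error was about 4–5%.
- **That the primary comparison loses the power shown in the table.** Those figures need a baseline value of the outcome, which is not listed for the Griffiths.

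The objection does not remove the central point. On every reading, observed differences decide which covariates enter. It is also true that the text describes no significance test for baseline balance, so the p<0.05 criterion here is only an assumption.

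**Conclusion.** The point holds and should be fixed, but it does not threaten the validity of the primary test on the likely reading. The model for every outcome is left to observed imbalance. For attitudes, parent practices and CES-D-10 the cost is about 3 to 13 percentage points of power (82 − 78 = 4 rounded, 3.4 unrounded, at r = 0.3; 93 − 80 = 13 at r = 0.6). This rests on the assumed 0.2 SD effect, selection threshold and correlations, and on full recruitment. For the Griffiths outcome the gain is a model fixed in advance and a little precision from other baseline covariates. The shrinkage to between 2.9 and 1.2 points arises only on the literal reading of 'at endline' and under assumed mediation strengths. It is a reason to reword the sentence, not a forecast of the result.

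**What to change.** Replace the covariate sentence in both the Data Analysis Plan and the closing Statistical analysis plan with:

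*Every impact model adjusts for a set of baseline covariates fixed before endline data are seen, whatever their balance (for example child age and sex, maternal education, housing/possessions score, baseline parent practices and CES-D-10), and for the randomisation structure (CHA). Endline attitudes, parent practices and CES-D-10 are each also adjusted for their own baseline value. No variable measured after randomisation is a covariate in an impact model; this does not apply to the separate mediation analysis.*

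The listed covariates are examples and the sponsor should settle the set. The deadline is tied to endline data because the document describes no blinding. CHA follows the Methods' description of four families per arm for each aide. The Implementation plan has supervisors assign families to aides after randomisation, so the sponsor should confirm that CHA was the stratum used and otherwise name the one that was.

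In the sample size paragraph, replace the aim of demonstrating equivalence with 'to describe the' intervention arms.

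The cost is wording only, since every variable named is already on the baseline form.
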